### Description of statistical methods

#### Primary outcome

The primary outcome of change in weight at 12 months will be analyzed by ITT BOCF for missing data. We will calculate mean and standard deviations of weight change at 12 months and compare the intervention arm with the control using analysis of covariance (ANCOVA) adjusting for baseline weight. This will be the primary analysis for the trial. A pre-specified sub-group analysis will examine the effect of gender, age (as a continuous variable), ethnic group, deprivation score derived from postcode and BMI. Residual plots will be used to examine model assumptions and where necessary transformations and/or bootstrapping will be used to address gross departure from normality. The possibility of GP effects will be explored via a random effects coefficient in the model.

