#### Randomization of participants

Participants will be randomized to a treatment arm at the baseline visit, which will be conducted at their own GP practice (see Measurement of outcomes [Visit 1, Baseline] for details). The RA will give eligible patients who are willing to participate in the trial an opaque A4 sealed envelope, which will contain a color-coded randomization card. The envelopes will be numbered in sequence. We will use block randomization of randomly sequenced blocks of 2 and 4 stratified by GPs, which will balance individual consulting styles. The trial statistician will be responsible for the production of randomization schedule, prior to recruitment.

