### Statistics and analysis

#### Number of participants

The primary outcome will be weight change at 12 months. The following figures assume a 70% follow-up achieved in the Lighten Up trial and use the (conservative) ITT BOCF figures. We assume that 30% in the CWMS arm will take up referral and achieve the mean loss seen in our trial of the same intervention at 1 year (3.46 kg with BOCF for missing outcome data) and that 10% in the control arm will try to lose weight and achieve the mean loss seen in the Lighten Up trial (1.16 kg). The Prospective Studies Collaboration showed that obese people observed over a few years lose a little weight on average, at about 50 g/year [2]. These assumptions give mean weight loss of 1.07 kg versus 0.16 kg. The standard deviation for weight change was about 6.0 kg in both our Lighten Up and the Jebb trial [14,15]. On these assumptions, with 90% power and 5% type I error, we would need to randomize 912 people to each arm: 1,824 in total.

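### Randomization is stratified by GP, but the primary ANCOVA leaves GP out, so its standard error is slightly too large; a GP random intercept should be in the primary model

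*Protocol article*

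**What the plan says.** Under Randomization of participants, the protocol article gives the allocation method: "We will use block randomization of randomly sequenced blocks of 2 and 4 stratified by GPs, which will balance individual consulting styles". GP is the only stratification factor named.

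Under Description of statistical methods, Primary outcome, the analysis will "compare the intervention arm with the control using analysis of covariance (ANCOVA) adjusting for baseline weight". The next sentence but one settles its status: "This will be the primary analysis for the trial". GP enters only at the end of that paragraph: "The possibility of GP effects will be explored via a random effects coefficient in the model".

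Under Secondary outcomes in the same part, 3-month weight change is analysed by the same baseline-weight ANCOVA, with no mention of GP.

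The sample size (Number of participants) has no GP term either. It rests on the assumed means ("These assumptions give mean weight loss of 1.07 kg versus 0.16 kg"), the spread ("The standard deviation for weight change was about 6.0 kg") and the conclusion "with 90% power and 5% type I error, we would need to randomize 912 people to each arm: 1,824 in total".

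**The concern.** The design treats GP as a likely source of variation in outcome; that is the stated reason for stratifying. Blocking within GP makes the two arms nearly equal in size for every GP. Differences between GPs in average weight change then largely cancel out of the comparison of arms, and the estimate varies less from trial to trial than under simple randomization.

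The primary ANCOVA does not take this into account. Without a GP term, between-GP variance stays in the residual, and the standard error is computed as if that variance still affected the comparison. The confidence interval is then a little wider than the design warrants, the test rejects a little less often than 5% under the null, and some power is lost.

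There is a second side to it. Each GP delivers both interventions, so the effect itself may differ between GPs. If it does, and the aim is to infer to GPs in general, a model with no GP term errs in the other direction.

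**Working it through.** **Inputs from the protocol article.** SD of weight change 6.0 kg; 912 per arm; 5% type I error (sidedness not stated; two-sided reproduces the stated size, one-sided would give 745 per arm). The assumed means are 0.3 × 3.46 + 0.7 × 0.05 = 1.073 kg and 0.1 × 1.16 + 0.9 × 0.05 = 0.161 kg, a difference of 0.912 kg (0.91 from the rounded means). Under Participant recruitment rate, 1,054 sessions at about six per GP give about 176 GPs, and 1,824 / 176 ≈ 10.4 participants each.

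**Assumed.** The documents give no GP ICC for weight change, so 0.01, 0.05 and 0.10 are used. Any gain from baseline-weight adjustment is ignored; the planned SD of 6.0 kg is taken as the total SD.

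**The plan's own figure.** n per arm = 2 × 6.0² × (1.960 + 1.282)² / difference². This gives 914 for 0.91 kg and 910 for 0.912 kg. The stated 912 is reproduced.

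**Intercept-only case: GPs differ in average outcome, the effect is constant.**

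- Reported SE, no GP term: 6.0 × √(2/912) = 0.281 kg.
- True SE under GP-stratified allocation: 6.0 × √(1 − ICC) × √(2/912). A model with GP reports this value.
- Type I error without GP: 2 × [1 − Φ(1.96 / √(1 − ICC))].
- Power without GP: Φ((0.912 − 1.96 × 0.281) / true SE).
- Power with GP: Φ(0.912 / true SE − 1.96).

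| Assumed ICC | Reported SE (kg) | True SE (kg) | Overstated by | Type I error, no GP | Power, no GP | Power, GP in model | Gain (points) |
|---|---|---|---|---|---|---|---|
| 0.01 | 0.281 | 0.280 | 0.5% | 0.049 | 90.2% | 90.4% | 0.2 |
| 0.05 | 0.281 | 0.274 | 2.6% | 0.044 | 90.6% | 91.5% | 0.8 |
| 0.10 | 0.281 | 0.267 | 5.4% | 0.039 | 91.2% | 92.8% | 1.6 |

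Gains are taken before rounding. Power without GP also rises with the ICC, because stratified allocation reduces the true SE whichever model is fitted.

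**In participants, at ICC 0.05.** Power with GP corresponds to 0.912/0.274 − 1.96 ≈ 1.370 on the normal scale. For the model without GP to match it, its reported SE must satisfy 0.912/SE = 1.96 + 1.370 × √0.95 ≈ 3.295, so SE ≈ 0.2767 kg. Then n = 72 / 0.2767² ≈ 940 per arm, 28 more than 912, or about 56 in total.

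**Simulation check.** Blocks of 2 and 4 within 176 GPs, ICC 0.10, no effect, 1,500 runs. Without GP the mean reported SE was 0.281 kg, the actual SD of the estimate 0.267 kg, and rejection 4.1%. With GP in the model (fitted as within-GP contrasts) rejection was 5.1%. At lower ICCs the effect is too small to separate from simulation noise at this number of runs.

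**If the effect varies between GPs.** With a between-GP SD of the effect τ, and inference to GPs in general, the variance gains about τ²/176. Take this alone (ICC 0) and hold the reported SE at 0.281 kg. For an assumed τ of 1.0 kg the true SE is √(0.0789 + 1/176) = 0.291 kg, so the reported SE is about 3% too small and type I error about 0.058. For τ of 1.5 kg it is 0.303 kg, about 7% and 0.069. These are slightly high, because the extra spread also enters the residual: at 1.5 kg the reported SE becomes √((72 + 2.25)/912) = 0.285 kg, about 6% too small.

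**The case against.** The strongest reply is that the protocol does not ignore GP. It foresees GP effects, names a random-effects approach, and says a statistical analysis plan will be written before recruitment starts. How that model is reported is detail an article may leave to that plan. This stands for the detail. It does not cover the primary model, which the article itself states without the stratification factor.

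It is also fair that the error is small and on the safe side. At an ICC of 0.01 it is 0.5% of the standard error, power stays at or above the planned 90% throughout, and every figure rests on an assumed ICC. All of that stands and limits the weight of the point.

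Three stronger readings are tempting, and the document supports none of them.

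- A reader might infer that two candidate primary results exist, with the choice open once both p-values are seen. The text names the baseline-weight ANCOVA and says "This will be the primary analysis for the trial"; the GP model is exploratory and nothing lets it replace the primary result.
- A reader might infer that the precision bought by stratifying is thrown away. The point estimate keeps the benefit of balance; only its reported standard error is somewhat too large. For the same reason it is wrong to compare power with GP against a constant 90.1% without it, or to count the loss at ICC 0.05 as 5% of 1,824, about 90 participants. That figure describes interval width, not the power lost.
- A reader might fear false positives. With a constant effect, type I error is below 5%. Only effect variation between GPs would raise it, and a random intercept alone would not correct that.

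**Conclusion.** The point holds as a modest mismatch between design and analysis. The primary model omits the only stratification factor and so reports a standard error that is 0.5% to 5.4% too large for assumed GP ICCs of 0.01 to 0.10, at a cost of about 0.2 to 1.6 percentage points of power. With a constant treatment effect the error is conservative, and 912 per arm needs no change.

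The sizes depend on the assumed ICC, a total SD of 6.0 kg and nearly balanced arms within GP. The reverse error, from effects that differ between GPs, depends on an assumed τ and on wishing to infer to GPs in general. It is a reason for a sensitivity analysis, not a demonstrated defect. This is an inexpensive improvement to make; it does not threaten the trial's conclusion.

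**What to change.** Under Primary outcome, state the primary model as 12-month weight change on arm and baseline weight with a random intercept for GP, retained whatever its estimated variance. This replaces the sentence on exploring GP effects. Use the same model for 3-month weight under Secondary outcomes.

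Name two sensitivity analyses: the baseline-weight-only ANCOVA, and a model with a random arm-by-GP slope. The second is needed because each GP delivers both interventions, and variation in effect between GPs would make the standard error too small.

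The cost is a few sentences in the analysis section. GP is already recorded as the stratification factor, so no new data and no larger sample are needed. The analysis plan should carry the same wording.

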#### Secondary outcomes

The difference in mean weight change at 3 months will be compared between the two treatment arms using ANCOVA adjusting for baseline weight with BOCF for missing data. Proportions of participants who achieve at least 5% or 10% weight loss at 12 months will be reported using descriptive statistics and the difference between two arms and 95% CI will be calculated. The costs of the two interventions will summarized as £ per kg and £ per kg/m^2^.

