**Methods/design:**

We propose a controlled trial where patients will be randomized to receive either the offer of help by referral to a weight management service and follow-up to assess progress, or advice to lose weight on medical grounds. The primary outcome will be weight change at 12-months. Other questions are: what actions do people take to manage their weight in response to the two GP intervention types? How do obese patients feel about GPs opportunistically discussing weight management and how does this vary by intervention type? How do GPs feel about raising the issue opportunistically and giving the two types of brief intervention? What is the cost per kg/m^2^ lost for each intervention? Research assistants visiting GP practices in England (n = 60) would objectively measure weight and height prior to GP consultations and randomize willing patients (body mass index 30+, excess body fat, 18+ years) using sealed envelopes. Full recruitment (n = 1824) is feasible in 46 weeks, requiring six sessions of advice-giving per GP. Participants will be contacted at 3 months (postintervention) via telephone to identify actions they have taken to manage their weight. We will book appointments for participants to be seen at their GP practice for a 12-month follow-up.

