### Secondary objectives

1) To examine the effect of an assistance-orientated versus advice-orientated intervention on mean weight change at 3 months *(*self-reported weight measure*).*

2) To examine the difference in the proportion of participants in each intervention group who achieved 5% and 10% weight loss at 12 months.

3) To examine how obese patients feel about discussing their weight with their GPs when they have visited for reasons other than their weight and how this may vary by intervention type.

4) To examine what actions people take to manage their weight, at 3 and 12 months, in response to the two types of GP intervention.

5) To examine how GPs feel about raising the issue of weight management opportunistically and giving the two types of brief intervention both before and after giving opportunistic interventions.

6) To assess the cost per kg, and per kg/m^2^, of the weight lost to the NHS for the two types of interventions.

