#### Secondary outcomes

2) The mean change in participants' weight from baseline to 3 months.

3) The proportion of participants who lose 5% and 10% of their initial weight at 12 months.

4) Costs of the two types of intervention to calculate the NHS cost per kg, and per kg/m^2^, lost.

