**After completion of participant recruitment** Similar to above, we will interview, via telephone, up to 30 participants based on the range of responses to the post-consultation questionnaire (see Visit 1) and ask them about why they responded as they did and whether another style of opportunistic intervention might engender a different reaction (Outcome #8). We will contact selected participants as soon as possible after the consultation to minimize forgetting.

##### 

**After trial completion** Costs of the two types of intervention will be assessed to calculate the NHS cost per kg, and per kg/m^2^, lost (Outcome #4).

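### Cost is planned as an average £ per kg lost for each arm; the control ratio has a denominator near zero, and no incremental cost per additional kg is stated

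*Protocol article*

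**What the plan says.** The cost measure appears in five places in the protocol article.

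- Abstract, Methods/design: "What is the cost per kg/m^2^ lost for each intervention", posed as a question.
- Secondary objectives, item 6: the cost per kg and per kg/m² "of the weight lost to the NHS for the two types of interventions".
- Secondary outcomes (endpoint list), item 4: "Costs of the two types of intervention to calculate the NHS cost per kg" and per kg/m² lost.
- Measurements of outcomes, after trial completion: the same measure again.
- Description of statistical methods, Secondary outcomes: "The costs of the two interventions will summarized as £ per kg" and per kg/m².

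The last of these does not itself say that the ratio is formed within each arm. The abstract settles that reading, because it asks for a figure for each intervention, and an incremental ratio is a single figure for a comparison. No section mentions a cost difference between arms or an incremental ratio.

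The planned denominators are in Number of participants: "These assumptions give mean weight loss of 1.07 kg versus 0.16 kg". The same section gives the spread: "The standard deviation for weight change was about 6.0 kg".

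**The concern.** A randomized trial estimates differences between arms. The other efficacy outcomes, weight change at 12 and 3 months and the 5% and 10% responder proportions, are all compared between arms; cost is not. Dividing each arm's cost by that arm's own mean loss has two consequences.

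First, the support arm is credited with its whole mean loss, including the part the control arm is expected to show anyway. Second, the control arm's cost is divided by a quantity that the plan itself places close to zero. That ratio can be very large, undefined or negative through sampling error alone. The kg/m² version has the same weakness, since it divides by the same small average change scaled by height.

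At stake is the reading of a secondary economic outcome. Someone weighing the support intervention against advice needs the extra cost of each extra kg lost. Two separate averages do not give that, and comparing them can mislead in either direction.

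**Working it through.** **Inputs from the article.** Number of participants: 30% uptake with 3.46 kg loss; 10% of controls try, with 1.16 kg loss; background loss 0.05 kg a year; SD 6.0 kg; 912 per arm; 90% power; 5% type I error (taken as two-sided). Background section: referral costs about £50 per patient.

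**The plan's own figures.**
- Support mean: 0.30 × 3.46 + 0.70 × 0.05 = 1.073 kg.
- Control mean: 0.10 × 1.16 + 0.90 × 0.05 = 0.161 kg.
- Sample size per arm: 2 × (1.960 + 1.282)² × 6² / 0.91² gives 914 (910 with the unrounded difference of 0.912). The stated 912 is reproduced and is not in question.

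The rounded 1.07, 0.16 and 0.91 kg are used below.

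**Denominators (no cost assumption needed).**
- Standard error of one arm's mean: 6/√912 = 0.199 kg.
- Control mean 95% CI: 0.16 ± 1.96 × 0.199 = -0.23 to 0.55 kg.
- Chance that the control mean is at or below zero: Φ(-0.16/0.199) = 21%.
- Between-arm difference: standard error 6 × √(2/912) = 0.281 kg; 95% CI 0.91 ± 0.55 = 0.36 to 1.46 kg. The chance of a value at or below zero is 0.06%.
- Share of the support arm's loss expected under control: 0.16/1.07 = 15%.

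**Ratios (cost assumptions needed).** Referral cost per randomized support patient is £50 × 0.30 = £15. The article prices neither the GP talk nor the review visit. Let c be an assumed talk cost per patient, equal in both arms, and r an assumed review cost per randomized support patient.

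- Support ratio: (15 + r + c)/1.07
- Control ratio: c/0.16
- Incremental ratio: (15 + r)/0.91, in which c cancels

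With r = 0:

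| c (assumed) | Support, £/kg | Control, £/kg | Incremental, £/extra kg |
|---|---|---|---|
| £1 | 14.95 | 6.25 | 16.5 |
| £2 | 15.89 | 12.50 | 16.5 |
| £3 | 16.82 | 18.75 | 16.5 |
| £5 | 18.69 | 31.25 | 16.5 |
| £10 | 23.36 | 62.50 | 16.5 |

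The two arm ratios are equal at c = 0.16 × (15 + r)/0.91:

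| r (assumed) | Order changes at c = | Incremental, £/extra kg |
|---|---|---|
| £0 | £2.64 | 16.5 |
| £5 | £3.52 | 22.0 |
| £10 | £4.40 | 27.5 |
| £20 | £6.15 | 38.5 |

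With the unrounded difference of 0.912 kg the first incremental figure is £16.4 and the last £38.4.

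**Sampling error.** 400,000 simulated pairs of arm means were drawn, with costs held fixed, c = £5 and r = 0. The control ratio was negative in 21%, positive but below the support ratio in 30%, and above it in 49%. Its central 95% range was about -£277 to £304 per kg. The incremental ratio's range was about £10 to £41 per extra kg.

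**The case against.** The strongest objection is that the analysis sentence is brief and does not rule out an incremental figure, and that a statistical analysis plan is promised. The choice of interval and the bootstrap are indeed details for such a plan, and their absence is no fault. The measure itself is a different matter: the abstract, objective, outcome list and analysis section all state it as cost per unit lost for the interventions. A plan that follows the article inherits it.

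A second objection is that little is lost. Mean losses by arm, the randomized weight difference and the costs of both interventions are all due to be obtained, so a reader could form the incremental point estimate. That stands, and it limits the importance of the point. It does not rescue the control ratio as a reported summary.

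Three stronger readings are tempting but unsupported.

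- A reader might infer that the two ratios can favour either arm in the same data. They cannot: for one dataset and one set of unit costs the order is fixed. It changes across assumed consultation costs or across samples.
- A reader might take £16.5 as the protocol's implied cost-effectiveness. It counts referral only and needs equal talk costs in both arms. The support arm also includes an offered one-month review, possible re-referral and possible orlistat, and the GP training covers a dedicated weight consultation in both arms.
- A reader might infer that adoption in the NHS hinges on this outcome. The rationale and discussion tie adoption to effectiveness; cost is a descriptive secondary outcome.

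**Conclusion.** The point holds for the stated cost measure. The instability of the control ratio follows from the article's own planning figures (0.16 kg, SD 6.0 kg, 912 per arm) with no cost assumption: a 95% CI of -0.23 to 0.55 kg and a 21% chance of a non-positive denominator. About 15% of the support arm's planned loss is loss expected without the referral.

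The change in ranking is conditional. It rests on £15 referral cost per randomized support patient, equal talk costs in both arms, and assumed talk and review costs that the article does not supply. On that footing the order changes at about £2.6 per patient, or about £3.5 to £6.2 if reviews add £5 to £20.

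The incremental ratio is stable only as far as the planned 0.91 kg difference is realized; a much smaller true effect would widen its interval too. This is a worthwhile correction to a secondary outcome. It is no threat to the primary result.

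**What to change.** State the cost outcome as the incremental NHS cost per additional kg, and per additional kg/m², lost: mean cost in the support arm minus mean cost in the control arm, divided by the corresponding difference in mean loss. Use the same intention-to-treat data with baseline observation carried forward as the primary analysis. Give a bootstrap interval that resamples participants within arm and keeps each participant's cost and weight change together. Report mean cost and mean loss by arm as separate quantities. If per-arm ratios are still shown, they should not be the summary measure. An acceptability curve is optional, since the article gives no willingness-to-pay value per kg.

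The change costs some wording and a small amount of extra analysis. It uses data already planned: GP contacts about weight, length of enrolment in the weight management service, and weight at 12 months. Unit costs are needed for the planned outcome in any case. The primary analysis and the sample size do not change.

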#### Non-efficacy outcomes

For participant’s reaction (assessed by two Likert scale questions) to the GP discussion of weight management when they visited for reasons other than their weight, total score will be calculated and compared between two arms using a t-test or a Mann–Whitney-U test if the data are too far from normality. The median for each question will be calculated and compared using a Mann–Whitney-U test.

Whether participants take any actions to manage their weight at 3 months and between 3 and 12 months following a brief opportunistic intervention reported by participants as a yes/no variable will be presented as frequencies and compared between the two arms using a chi-square test. What actions participants took will be coded as a three-category variable (that is, effective action, some action and no action) and compared for the difference between arms using proportional odds logistic regression.

Reactions of GPs to raising the issue of weight management opportunistically and giving the two types of brief intervention will be summarized by presenting the frequencies of each response to question 1, 2 and 7 of GP post-trial questionnaire part 2 in a bar chart. Total score will be calculated by summing questions 3 and 4 for the reaction of GPs to advise to lose weight and summing questions 5 and 6 for the reaction of GPs to offering support. These two total scores will be compared using a paired t-test.

Only summary statistics will be presented by intervention arms for the following non-efficacy outcomes:

• Change from pre-trial to post-trial in the frequencies of each response to the first 11 questions of GP questionnaire part 1 and the mean percentage for question 12 regarding GP attitudes to making opportunistic interventions and treating obese people.

• Frequency of each category of reasons for not trying to lose weight given by participants.

• Total number of CWMS sessions taken.

The qualitative data on responses to the intervention (as identified in Data handling and record keeping below) will be analyzed using framework analysis. This approach is a relatively quick method of qualitative enquiry that allows deductive exploration based on the aims and objectives of the interview. A thematic framework for analysis will be constructed prior to interview and unanticipated themes arising during interview will be added to the framework as appropriate. Data will be sorted and summarized under theme and subtheme headings from which the range and diversity of attitudes and experience will be summarized and explanatory linkages explored.

